## Methods

### Study design

This Type-II Hybrid Implementation-Effectiveness study [40] will primarily test implementation strategies on provider adoption and implementation quality. We will use a cluster RCT design to test the effectiveness of the implementation models on provider- and client-level outcomes with a mixed-methods approach. Specifically, this three-arm trial compares the three multi-component strategies for implementing depression care guidelines: (1) UI arm which includes basic depression care capacity workshops, limited technical assistance, and toolkits, 2) ES arm which includes all components of UI and additional structured clinical supervision from provincial and district supervisors, and 3) CELC arm which includes all components of ES, combined with the activation of a community-wide network of providers and stakeholders who are implementing continuous QI strategies (Fig. 1). The primary outcome is to compare the fidelity of MCCD on three implementation models using the RE-AIM framework [41], which will be assessed based on implementation outcomes (**R**each, **A**doption, **I**mplementation quality, and **M**aintenance) and provider and client-related outcomes (**E**ffectiveness) (Table 1). The secondary outcome is to assess factors associated with barriers and facilitators of quality implementation, which may serve as mechanisms for implementing additional supports for the ES and CELC arms. The tertiary outcome is to evaluate the incremental cost-effectiveness which quantifies the cost savings to policymakers when integrating various strategies for task-shifting depression care into primary care settings.

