### Outcome evaluation and analysis for AIM 1 (Fidelity to MCCD)

#### Power analysis

We used the pwr package in R software to determine the sample size and estimate power to detect a small eta-squared effect size of 0.025 with an expected intra-class correlation coefficient (ICC) of 0.2. Our primary outcome analyses focus on the 12-month timepoint, we will enroll 10 providers per site resulting a total of 360 providers (180 CHS staff and 180 non-CHS staff) across 36 sites in order to achieve 80% power to detect the small effect size. We also enroll 18 clients per site per phase which results in a total of 648 clients over two phases. With client outcome, power calculations assume near-normal outcomes with a two-sided Type I error of 0.05, this design has 80% power to detect small effects (small Cohen’s d effect size of 0.14 for a 3 × 3 contingency table chi-square test, given 4 degrees of freedom [(3 intervention groups {UI, UI + ES, UI + ES + CELC} − 1)*(3 outcome levels of PHQ-9 score change from baseline to 6 months {positive change, no change, negative change} − 1)]).

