#### RE-AIM outcomes

According to the RE-AIM framework, for an intervention to have an impact, it must **Reach** the population in need of the service, demonstrate **Effectiveness**, be **Adopted** by the system and providers, be **Implemented** with quality, and be **Maintained** or sustained over time. The indicators’ description as well as data sources were presented in detail in Table 1. A cascade of MH care will be built based on these indicators (Fig. 2). Mean and standard deviation will be presented without the normality violation, otherwise, median and interquartile ranges will be used. Independent ANOVA and/or Kruskal-Wallis test will be applied to assess differences stratified by intervention arms.

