#### Provider selection

Based on power considerations, we will recruit 10 providers from each CHS and 360 across the study, including five primary care providers (usually physician assistants or nurses) from the CHS and five (usually VHWs) working with the CHS, totaling 180 CHS providers and 180 non-CHS staff. Providers will be recruited post-enrollment but pre-CHS randomization at each CHS.

We will use a repeated measure design to conduct online self-reported surveys with CHS and non-CHS providers at baseline (before the workshop, during the study enrollment meeting), 6-, 12-, and 24-month follow-up. All follow-up surveys will be distributed and collected by the research coordinator within a one-week period of each data collection time point. The survey will assess the following categories: socio-demographic characteristics (e.g., year of birth, gender, education, number of years working in health system), MH training, depression care attitude scale using the adapted Evidence-Based Practice Attitude Scale (EBPAS) [50], working environment using the Implementation Climate Scale (ICS) [51], CHS head’s leadership using the Implementation Leadership Scale (ILS) [52], depression care activities (e.g., frequency of depression screening and depression treatment offered) and skills, depression stigma [53] and depression knowledge quiz including 20 multiple-choices questions which covers all training topics.

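### Provider-level RE-AIM indicators are to be compared by an ANOVA or Kruskal-Wallis test with no CHS term, so at the plan's ICC a nominal 5% test of Adoption would reject falsely in about one trial in three

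*Protocol article*

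**What the plan says.** The protocol article sets up a cluster trial in its Study design section: "We will use a cluster RCT design to test the effectiveness of the implementation models on provider- and client-level outcomes". Allocation is by CHS, with 6 per arm in each of two provinces, hence 12 per arm and 36 in all (Study site eligibility and recruitment). The Power analysis section assumes "an expected intra-class correlation coefficient (ICC) of 0.2" and a "small eta-squared effect size of 0.025", and sizes the provider sample as follows: "we will enroll 10 providers per site resulting a total of 360 providers (180 CHS staff and 180 non-CHS staff) across 36 sites".

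For comparing arms on the RE-AIM indicators, the section RE-AIM outcomes names one approach: "Independent ANOVA and/or Kruskal-Wallis test will be applied to assess differences stratified by intervention arms". It says nothing about the CHS as a level, about aggregation to CHS values or about variance correction.

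A model that allows for clustering appears only in the Client outcomes section. There a generalised linear mixed model is given for binary outcomes, namely improvement and remission. Table 1 takes Adoption from a provider self-report survey and competence from supervisors' assessments of providers. Neither is given any other between-arm test.

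**The concern.** Providers in one CHS share a head, a workload, a supervisor and the allocated strategy, so their answers are correlated. The plan accepts this by assuming an ICC of 0.2. A one-way ANOVA or Kruskal-Wallis test on 360 providers counts them as 360 independent units, although only 36 units were randomised. Its reference variance is therefore too small, and differences between CHSs that arise by chance look like differences between arms.

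The Study design section says the trial primarily tests the strategies on provider adoption and implementation quality, so the affected comparisons are central ones. The error favours finding differences between arms. The article intends its results to inform decisions on scale-up, so a false positive could support a more resource-intensive strategy that does no better than usual implementation.

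**Working it through.** **Inputs.** 3 arms and 12 CHSs per arm (Study site eligibility and recruitment); 10 providers per CHS, of whom 5 are CHS staff (Power analysis; Provider selection); ICC 0.2 (Power analysis). The level of 0.05 is stated for the client outcomes and assumed here for providers.

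**The plan's own provider figure.** The plan enrols 360 providers "in order to achieve 80% power to detect the small effect size". For a one-way ANOVA without clustering, the noncentrality is 360 × 0.025/0.975 = 9.23, and the power on 2 and 357 degrees of freedom is 77.8%. That does not reproduce 80% exactly (80% needs 381 providers), but it is close. With the design effect 1 + 9 × 0.2 = 2.8, the effective sample is 360/2.8 = 129 and power is about 34%. The stated power is therefore near what an analysis of 360 independent providers would give. This bears on which unit the test has in mind; it is not itself the point made here.

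**False-positive rate of the stated test.** Take m providers per CHS, ICC ρ, total variance 1 and no arm effect.

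- Design effect: DE = 1 + (m − 1)ρ.
- The between-arm mean square has expectation DE.
- The within-arm mean square has expectation [33 × DE + 36(m − 1)(1 − ρ)]/(36m − 3). For m = 10 and ρ = 0.2 this is (33 × 2.8 + 324 × 0.8)/357 = 351.6/357 = 0.985.
- The F ratio is thus centred near 2.8/0.985 = 2.84 instead of 1.

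With 2 numerator degrees of freedom, the rejection rate is approximately P(χ²₂ > 5.99/DE) = exp(−5.99/(2 × DE)). It was checked with 2,000,000 draws from the distribution of the F ratio.

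| Providers per CHS | ICC | DE | Approximation | ANOVA, from draws |
|---|---|---|---|---|
| 10 | 0.2 | 2.8 | exp(−1.070) = 34.3% | 34.7% |
| 5 | 0.2 | 1.8 | exp(−1.664) = 18.9% | 19.2% |
| 10 | 0.1 | 1.9 | exp(−1.576) = 20.7% | 20.8% |
| 10 | 0.05 | 1.45 | exp(−2.066) = 12.7% | 12.7% |
| 10 | 0.01 | 1.09 | exp(−2.748) = 6.4% | 6.4% |

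Kruskal-Wallis does no better. In 10,000 simulated trials at ICC 0.2 it rejected in 33.7% with 10 per CHS and in 18.2% with 5. A further simulation of 3,000 trials with 10 per CHS gave 33.3% (ANOVA) and 32.9% (Kruskal-Wallis) at ICC 0.2, and 14.1% and 13.6% at ICC 0.05.

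**Check of the remedy.** An ANOVA on the 36 CHS means, on 2 and 33 degrees of freedom, rejected in 5.1% of the 10,000 trials with 10 per CHS at ICC 0.2.

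**The case against.** The sentence names no unit of analysis. Many Table 1 indicators are counts or percentages: people screened, acceptance of behavioural activation, prescriptions, completion and dropout. Means or medians of a total make most sense across sites, and an ANOVA on 36 CHS values keeps its level. This stands for those indicators. It does not rescue Adoption or individually rated competence, which are provider-level measures in a study sized on 360 providers, and no aggregation is mentioned.

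A reader might infer that the 33-35% applies to every RE-AIM outcome. The documents do not support that. The figure needs 10 individually analysed providers per CHS, which fits provider-survey Adoption. Session ratings and competence concern at most the 5 CHS staff. They also rest on supervisors, and structured supervision is part of the two enhanced arms, so the 19% presumes that such ratings exist in all three arms.

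A reader might also extend the calculation to 18 clients per CHS and get about 51% at ICC 0.2. That borrows an ICC stated beside the provider effect size; none is given for clients. The same calculation gives about 8% at ICC 0.01, 20% at 0.05 and 33% at 0.1. Improvement and remission have their own model and are outside the point.

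The provider survey is repeated ("We will use a repeated measure design to conduct online self-reported surveys with CHS and non-CHS providers"), and one might fault the test for ignoring this. However, the Power analysis section puts the primary analysis at 12 months, where each provider contributes one value, so that complaint carries little weight.

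Randomisation was within matched sites in a district and balanced on high and low performance. So far as matching explains between-CHS variance, an unadjusted test rejects less often than calculated. The amount is unknown.

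Finally, an article condenses, and a fuller plan may say more. But this article does not leave the test open: it names one, and that one conflicts with its own design.

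**Conclusion.** The point holds for RE-AIM indicators analysed at provider level. There the named test is wrong for the design, as distinct from under-described. Under no arm effect, a nominal 5% test rejects in about 33-35% of trials for Adoption with 10 providers per CHS at the plan's ICC of 0.2. It rejects in about 19% where only the 5 CHS staff are rated, and in about 13-14% with 10 per CHS at ICC 0.05. These rates assume equal cluster sizes, a normally distributed outcome, 12 CHSs in each of three arms and matching that explains none of the between-CHS variance. No client-level figure can be fixed without an assumed ICC. The matter should be corrected before analysis, because it concerns comparisons that the trial primarily makes and the correction is cheap.

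**What to change.** Replace the ANOVA/Kruskal-Wallis sentence in the RE-AIM outcomes section with two rules.

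1. **Provider-level indicators, and any client-level indicator analysed individually:** compare arms at 12 months with a linear or generalised linear mixed model. Include a CHS random intercept, the randomisation strata as fixed effects and small-sample degrees of freedom suited to 36 clusters (for example Kenward-Roger or Satterthwaite for the linear model). Add the baseline value where one is collected, as in the provider survey. Add a provider random intercept only if several survey waves are modelled together.
2. **Indicators with one value per CHS:** analyse the 36 CHS values, adjusted for the strata. Any rank test is applied to CHS-level summaries.

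State for each Table 1 indicator which rule applies. The cost is wording and a little more programming, with no new data. Confidence intervals will be wider, and correct.

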#### Provider selection

Based on power considerations, we will recruit 10 providers from each CHS and 360 across the study, including five primary care providers (usually physician assistants or nurses) from the CHS and five (usually VHWs) working with the CHS, totaling 180 CHS providers and 180 non-CHS staff. Providers will be recruited post-enrollment but pre-CHS randomization at each CHS.

We will use a repeated measure design to conduct online self-reported surveys with CHS and non-CHS providers at baseline (before the workshop, during the study enrollment meeting), 6-, 12-, and 24-month follow-up. All follow-up surveys will be distributed and collected by the research coordinator within a one-week period of each data collection time point. The survey will assess the following categories: socio-demographic characteristics (e.g., year of birth, gender, education, number of years working in health system), MH training, depression care attitude scale using the adapted Evidence-Based Practice Attitude Scale (EBPAS) [50], working environment using the Implementation Climate Scale (ICS) [51], CHS head’s leadership using the Implementation Leadership Scale (ILS) [52], depression care activities (e.g., frequency of depression screening and depression treatment offered) and skills, depression stigma [53] and depression knowledge quiz including 20 multiple-choices questions which covers all training topics.

#### Client outcomes

Clients identified with depression as part of routine depression screening at CHS will be recruited to participate in the client outcomes survey study across two implementation support phases. Eligible clients included those who are (1) new to the program, (2) aged 18–65, and (3) screened positive for depression using the PHQ-9 (score > 9). Those with a risk for severe mental illness (psychosis, mania, and substance abuse) will be excluded from the Client Study Cohort and referred to the provincial psychiatric hospital, per the stepped care model mentioned in the intervention description. Based on a depression screening rate of 20% and a research acceptance rate of 75% from our prior work [20], we expect CHS staff to screen 2,200 clients to consent 324 participants across each province for each Client Study Cohort. Across the total sample of 648 clients in each implementation phase. We will request permission from participants to link survey data to client administrative and clinical data.

The effectiveness on the client outcome will be measured based on the client’s improvement (defined as a 50% reduction in PHQ-9 score between the first and last BA session) and client’s remission (defined as the last PHQ-9 score less than 5). We will conduct an intent-to-treat analysis (e.g., those who are lost to follow-up are considered neither improved nor remised) in order to ensure the randomization process. A generalized linear mixed-effects model will be used for binary outcomes with a binominal family distribution and logit link. Exponentiating the fix-effect coefficients for treatment conditions will result in estimates of the odds ratio regarding the effect of treatment condition on depression symptomatology. These models will be adjusted for the clustering effects across multiple levels of hierarchical data structure (e.g., providers, clients) and the UI intervention will be used as a reference group.

In addition to the PHQ-9, our client cohort study will collect additional information at baseline and 6-month surveys, including socio-demographic information (e.g., age, gender, education, marital status, household characteristics), house and general socio-economic status (e.g., house ownership, monthly expense, social standing), employment and business activities (e.g., employment status, regular source of income, personal and family monthly income), health functioning using the World Health Organization Disability Assessment Schedule 2.0 (WHO-DAS 2.0) [54], quality of life (Q-LES-Q-SF) [55], self-efficacy using the adapted Adult AIDS Clinical Trials Group (AACTG) [56], depression stigma [53] and Behavioral Activation for Depression Scale (BADS-SF) [57], social support using the Medical Outcomes Study (MOS) [58], social capital, family environment using the McMaster Family Assessment Device (FAD) [59] and CHS Client Satisfaction Questionnaire (CSQ) [60].

### Outcome evaluation and analysis for AIM 2

The secondary outcome is to assess factors associated with barriers and facilitators of quality implementation. Implementation progress, barriers, and facilitators will be captured using mixed methods, which will combine monthly implementation data with qualitative interviews for high and low-performing sites (high and low adopters) in each province for both phases. Interviewers should review the implementation data table before conducting qualitative interviews to construct the “implementation story” based on the monthly implementation data which is extracted from clinical records/logs and training records. Interviewers will interview all providers, leaders, and supervisors engaged in depression care for each site, but not all questions need to be asked for each provider. We expect to interview approximately 5 participants (2–3 providers, 1 leader, and 1 supervisor) to construct the implementation story, including milestones, timelines, barriers, and facilitators to implementing and sustaining depression care. We also assess their feedback regarding toolkits and materials, training, supervision support, and learning collaboration to identify the strengths and weaknesses of our program. These interviews will be conducted at the end of each phase.

Qualitative data will be transcribed verbatim in Vietnamese and translated into English. This process will be conducted by a bilingual doctoral student in community health and health policy ([name]) who had a master’s degree in Epidemiology to ensure the conceptual equivalence of translated transcriptions. All transcripts and descriptors will be imported to Dedoose [61] for data management and analysis. The grounded theory analysis will be implemented to identify themes during the iterative coding process. Further, two research assistants will independently code all transcripts to ensure interrater reliability. All notes will be added to the analytic memos whenever a new code emerged. The research assistants will consistently revise the codebook and re-group the codes used if necessary.

### Outcome evaluation and analysis for AIM 3

Activity-based costing will be used to assess costs associated with all activities involved in the implementation strategy interventions and depression care services, inclusive of (i) the personnel involved, (ii) the infrastructure and physical space utilized, (iii) equipment, (iv) consumables such as medications and print-outs, and (iv) overhead and other indirect costs such as utilities (Table 2). This will also entail an assessment of client costs, in order to determine the full cost of the program from a societal perspective. Team members will gather cost information from electronic financial systems, payroll, facility ledgers, and price lists to ascertain the cost of various medical equipment, infrastructure, personnel and consumables. Salaries will be quantified to include fringe benefits for relevant personnel involved in the study—including the provincial and district supervisor, CHS and non-CHS staff, and our implementation partners. The cost of medical equipment, which will be obtained from facilities records, will be annualized based on linear depreciation over estimated useful lifespan.

**Table 2 Tab2:** Identification of Main Costs for Each Group of Participants

Measures of Direct Cost	Collected	Source	Valuation

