**Implementation Quality**		
Adherence	Degree of fidelity to the content of the BA sessions	Supervision Ratings
Quality	General quality implementing the BA sessions	Supervision Ratings
Depression Care Competence	Depression care competence rated by supervisors	Provider Competency Assessment
Treatment Completion	# and % of clients with 4 or more sessions	Session Progress Note
Treatment Dropout	# and % of clients with 1 or less sessions	Session Progress Note
**Effectiveness**	Pre- and post-treatment differences; PHQ-9 Survey data	PHQ-9 Treatment Data and Survey Data
Client Improvement	50% reduction in PHQ-9 score	PHQ-9 – Session Scores (first and last)
Client Remission	Last PHQ-9 < 5	PHQ-9 – Session Score (last)
**Maintenance**	Independent implementation is considered an early sign of maintenance or penetration	Active Implementation Support; Transitional Support

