### Arm 1: usual implementation (UI)

#### Staff

All CHS staff will attend a series of hybrid depression care capacity training which includes a total of five weeks of online self-learning modules, four in-person workshops and five online Zoom-based webinars (totaling approximately 50 hours of hybrid training), implementation toolkits (e.g., BA manual, program implementation manual, clinical forms, workflow, clinical flow charts, health education materials), and limited technical support from national-level training team (e.g., initial program setup, observing depression screening and assessment) prior to the official rollout of the depression care program. All CHS staff will be trained to document service delivery using documentation tools, such as the screening log, screening and clinical intake assessment forms, session notes, and other clinical support forms. These forms will serve as the program’s administrative records. Additionally, non-CHS staff will attend a MH education and community outreach training which include two-week online learning on Moodle system and two-day in-person workshop. All non-CHS staff will be trained on promoting and educating MH in the community, screening for depression using the PHQ-4 as well as referring at-risk people and supporting care navigation to ensure successful linkages to CHSs.

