### Arm 3: community-engaged learning collaborative (CELC)

CHS Providers will receive all components of the ES group, plus a new quality improvement (QI) strategy: CELC. The CELC meetings will be based on the community engagement and planning implementation intervention model in Community Partner in Care [35, 38, 46] and the CELC from the Institute for Healthcare Improvement (IHI) Chronic Care Model [47]. The IHI model includes key components like forming a planning group that decides on a mutual set of target objectives, identifies specific areas for change, prepares pre-work with participants, implements in-person learning sessions. During CELC meetings, CHS staff and their supervisors learn about QI approaches and strategies on how to provide effective ongoing support to clients (e.g., phone calls, visits, messaging via apps, social media). Between each learning session, the CELC groups engage in Plan-Do-Study-Act (PDSA) cycles in which they brainstorm and decide on brief CHS-level interventions aiming to improve certain clinical processes at the CHS or meeting certain treatment benchmarks and assess their impact afterward [48]. Because of the resource intensity of the IHI model, we will adapt and simplify the approach in partnership with the community-academic-policy council to develop a learning collaborative (LC) that is feasible and culturally appropriate for the Vietnam health and social system. For example, QI learning collaboratives tend to last between 1 and 2 years [49], but we will only have nine meetings that are strategically placed to maximize implementation support.

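### Client improvement and remission are scored from first and last BA-session PHQ-9, with loss counted as failure: attendance differences between arms can read as symptom benefit, and the power calculation uses a different endpoint

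*Protocol article*

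**What the plan says.** All references are to the protocol article.

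- **Client outcomes**: improvement is "defined as a 50% reduction in PHQ-9 score between the first and last BA session" and remission is "defined as the last PHQ-9 score less than 5". The analysis is called intent-to-treat, with the rule that "those who are lost to follow-up are considered neither improved nor remised". A logistic mixed model then estimates the effect of treatment condition on depression symptoms.
- **Table 1**: the source for improvement is "PHQ-9 – Session Scores (first and last"), and for remission the last session score. The parent Effectiveness row also names PHQ-9 survey data, but neither binary endpoint is defined on them. Under Implementation Quality, completion (4 or more sessions) and dropout (1 or fewer) are separate outcomes. BA acceptance is a Reach indicator.
- **Power analysis**: the client calculation is for "3 outcome levels of PHQ-9 score change from baseline to 6 months".
- **Survey data**: "In addition to the PHQ-9, our client cohort study will collect additional information at baseline and 6-month surveys". The Abstract says the clients are surveyed at both times for depression severity.
- **Arms**: ES adds supervision that includes observing BA sessions with feedback. CELC adds improvement cycles "aiming to improve certain clinical processes at the CHS or meeting certain treatment benchmarks". On records, "All CHS staff will be trained to document service delivery using documentation tools", and session notes are among those tools.

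**The concern.** The endpoint that is meant to show whether clients got better depends on whether, and how long, they attended BA, and on whether the last session score was recorded. The extra support in ES and CELC is aimed at BA delivery. If that support raises attendance or improves the forms and does nothing more, the session-based response and remission rates still rise. The trial would then count a retention gain twice: once under completion and dropout, where it belongs, and again as an effect on depressive symptoms.

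The last score is also taken at a different time since baseline for each client. The Discussion describes the psychotherapy as lasting 2 to 3 months, so the last session would normally come before the 6-month point on which the client sample size rests.

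**Working it through.** **1. The plan's own power figure.** Inputs from Power analysis: N = 648, effect size 0.14, 3 × 3 chi-square, 4 degrees of freedom, alpha 0.05. The noncentrality is N·w². At w = 0.14 it is 648 × 0.0196 = 12.70 and power is 82.7%. Power of 80.0% is reached at w = 0.1357, which rounds to 0.14. The stated figure reproduces, and it belongs to baseline-to-6-month change, not to the first-to-last-session endpoint.

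**2. Who can score under the stated definitions.**
- No BA session: no first or last score. Such clients are to be expected. BA acceptance is itself an outcome. Eligibility is PHQ-9 above 9 with no stated upper limit, while the stepped-care text offers BA first to scores of 10 to 20. The text does not say whether a never-starter counts as lost to follow-up.
- One session: first equals last, so the reduction is 0% and improvement is impossible.
- Two or more sessions, then dropout: a last score exists, but the text does not say whether that score or the failure rule applies.

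**3. Effect of missing = failure.** Let m be the share without a usable last score, s the response among scored clients and u the response among unscored clients.

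- Scored rate = s(1 − m)
- True rate = s(1 − m) + u·m

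Assumed values (the documents give none): s = 50%; m = 30% in the usual implementation (UI) arm and 10% in a supported arm. The scored rates are 0.5 × 0.7 = 35% and 0.5 × 0.9 = 45%, so OR = (0.45/0.55)/(0.35/0.65) = 1.52. How much of that is real depends on u:

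| u | True rate, UI | True rate, supported | True OR | Scored OR / true OR |
|---|---|---|---|---|
| 50% | 50% | 50% | 1.00 | 1.52 |
| 25% | 42.5% | 47.5% | 1.22 | 1.24 |
| 10% | 38% | 46% | 1.39 | 1.09 |
| 0% | 35% | 45% | 1.52 | 1.00 |

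With m = 20% versus 10% and u = s = 50%, the scored rates are 40% and 45%, OR = 1.23. With equal true response of 40 to 60% and gaps of 10 to 20 points in the usable-score share, the scored OR runs from 1.20 to 1.64.

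**4. Chance of a misleading significant result.** Take the first row (35% versus 45% scored, no true difference), 648/3 = 216 clients per arm and 18 per site. The chance of a significant result favouring the supported arm is:
- 56% if clients are independent;
- 34% at an assumed ICC of 0.05 (design effect 1 + 17 × 0.05 = 1.85);
- 17% at the ICC of 0.2 named in Power analysis (design effect 4.4).

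The nominal rate in that direction is 2.5%.

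**The case against.** Several stronger readings are tempting, and the documents do not support them.

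- **That the plan ignores the survey PHQ-9.** It does not: Table 1 names survey data under Effectiveness. How they will be modelled may be set out in a document not shown here, and silence on that is no fault. What stands is that both stated binary endpoints, and the only model described for them, use session scores.
- **That the intent-to-treat label is plainly contradicted.** Clients lost to follow-up stay in the denominator as failures. What stands is an undefined case, the never-starter, and a rule that ties the score to attendance.
- **That providers inflate scores because their clients' results are reviewed.** The ES text does not describe review of client PHQ-9 results, and the benchmark wording belongs to CELC only and does not name the PHQ-9. Staff keep the session records, but who completes or scores the PHQ-9 is not stated. Nor is masking of the survey collectors, so the survey has no documented masking advantage.
- **That the whole OR of 1.52 is spurious.** This requires unscored clients to respond as often as scored ones. If they respond at 10%, the true OR is 1.39 and most of the difference is real. In a hybrid implementation trial, symptom benefit gained through better retention is part of the strategy's effect. This objection stands in full as to size. It does not rescue the endpoint, because session data alone cannot separate the two parts.

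**Conclusion.** The point holds in its limited form. As written, the effectiveness endpoint cannot be met by a one-session client, is undefined for a never-starter, is timed by attendance, and differs from the endpoint that was powered. Differences between arms in attendance or record-keeping can therefore be read as symptom benefit.

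The size of any bias is unknown. The figures above are illustrations resting on assumed missing-score shares and assumed response among unscored clients. Within them, the excess in the odds ratio runs from nothing (unscored clients never respond) to a factor of 1.52 (they respond as often as the rest). No provider scoring bias and no masking defect is claimed.

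This should be corrected before analysis. It affects one RE-AIM domain, and the data needed are already planned.

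**What to change.** In Client outcomes and Table 1, make the PHQ-9 at the 6-month survey the effectiveness endpoint, sought from every enrolled client regardless of BA attendance. Define response as a reduction of at least 50% from the baseline survey and remission as PHQ-9 below 5 at 6 months. Analyse the continuous score as well, adjusted for baseline PHQ-9. State which form is the main one and align Power analysis with it.

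Handle survey non-response by multiple imputation that uses baseline and session data, with missing = failure as a sensitivity analysis. With a single follow-up survey, a mixed model under missing-at-random gives limited protection against loss that differs by arm, so the session data are worth using in the imputation. Keep first-to-last-session change as a process indicator beside completion and dropout, and state how clients with no session or one session are scored on it.

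The cost is endpoint and analysis wording, since the survey PHQ-9 is already planned at both times. If the chosen form is not the three-level change, the power statement must be redone. Two downsides remain: a single 6-month time point may not reflect response at the end of therapy, and survey loss still has to be handled.
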